### Registration

Patients will be enrolled at POD 1. An eligibility report form will be sent to the registration center (APO PLUS STATION Co., Ltd, Tokyo, Japan). Eligible patients will be centrally randomized to either the DKT group or non-DKT group at the registration center using a computer random number generator with the minimization method for TNM stage, tumor location, and age. Information on the necessary follow-up evaluations will then be sent from the registration center. A flow diagram of this study is shown in Fig. 2.

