### Sample size determination

The sample size calculation is based on a primary endpoint, GIQLI. The GIQLI questionnaire containing 36 questions each with five response categories. The responses to questions are summed to give a numerical score (0–128 points). A previous report [9] indicates that the mean ± standard deviation (SD) change in the GIQLI score between two measurements before and 2 weeks after laparoscopic cholecystectomy in 194 patients was 17 ± 20.7 points. Therefore, the clinically significant mean difference in the GIQLI score is set at 20 with a SD of 20. Using a power level of 80% and a two-sided significance level of 5%, 32 patients (16 patients in each group) are required to show a difference between the DKT and non-DKT groups. Therefore, we determined that 40 patients (20 patients in each group) are needed to endure 20% dropout of patients from this trial.

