### Statistical analysis

All analyses will be performed under the intention-to-treat principle. However, patients will be excluded from the analyses if they are proved to be ineligible after enrollment. Both primary and secondary endpoints will be compared between the DKT group and the non-DKT group. A two-tailed *P* value less than 0.05 is considered statistically significant. For continuous variables, the *t* test will be used when continuous variables follow a normal distribution, whereas the Wilcoxon rank-sum test will be used when continuous variables follow a non-normal distribution. For categorical variables, the chi-square test or Fisher’s exact test will be used according to the cell count.

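### Allocation is minimised on TNM stage, tumour location and age but every stated test is unadjusted, so each test is conservative if those factors are prognostic

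*Protocol article*

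**What the plan says.** Under Registration, the protocol article allocates patients centrally, "using a computer random number generator with the minimization method for TNM stage, tumor location, and age". It does not say why these factors were chosen, how many levels each has, or what random element the minimisation uses.

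Under Statistical analysis, "Both primary and secondary endpoints will be compared between the DKT group and the non-DKT group". The tests are then named. Continuous endpoints get a t test if they are normally distributed; if not, the article says that "the Wilcoxon rank-sum test will be used when continuous variables follow a non-normal distribution". Categorical endpoints have their own rule, namely that "the chi-square test or Fisher’s exact test will be used according to the cell count". None of these tests, as named, includes a minimisation factor, and the article mentions no adjusted, stratified or re-randomisation analysis.

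The Sample size determination section also works without covariates: "the clinically significant mean difference in the GIQLI score is set at 20 with a SD of 20".

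**The concern.** Minimisation makes the arms more alike on its factors than simple randomisation would. A two-sample test takes its standard error from the whole spread of outcomes within each arm, as if balance on those factors had been left to chance. If the factors predict the outcome, that spread includes variation that can no longer separate the arms. The reported standard error is then larger than the true one, confidence intervals are too wide and P values too large. What is at stake is precision in a 40-patient trial that, by its own Discussion, may be too small and is meant to guide a full-scale trial.

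**Working it through.** **1. The plan's own figure.** Inputs from Sample size determination: difference 20, SD 20, two-sided 5%, power 80%, dropout 20%.

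- n per arm = 2 × (1.960 + 0.842)² × 20² / 20² = 15.7, so 16 per arm and 32 in total.
- 32 / (1 − 0.20) = 40.

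Both stated figures are reproduced. Power at 16 per arm is 0.807 by the normal approximation. By the exact noncentral t it is 0.781 at 16 per arm and 0.869 at 20 per arm.

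**2. Analytic check, perfect balance.** Let R² be the share of outcome variance explained by the three factors. The unadjusted test reports a standard error of about 20 × √(2/20) = 6.32 at 20 per arm, but the true one is smaller by the factor √(1 − R²). Type I error is therefore 2 × [1 − Φ(1.96 / √(1 − R²))]:

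- R² = 0.1: 1.96 / 0.949 = 2.07, giving 3.9%
- R² = 0.2: 1.96 / 0.894 = 2.19, giving 2.8%
- R² = 0.3: 1.96 / 0.837 = 2.34, giving 1.9%

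**3. Simulation with realistic, imperfect balance.** Assumptions, none of them given in the document: factors with 3, 2 and 2 levels contributing equally, preferred arm chosen with probability 0.8, normally distributed outcomes with total SD 20, and R² from 0 to 0.3. The adjusted analysis is a linear model with treatment and the three factors. There were 3,500 trials per setting at N = 40, so the Monte Carlo standard error near 5% is √(0.05 × 0.95 / 3500) = 0.4 points.

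| R² | Reported SE | True SE | Ratio | Type I, t | Type I, Wilcoxon | Type I, adjusted | Power, t | Power, adjusted |
|---|---|---|---|---|---|---|---|---|
| 0 | 6.26 | 6.30 | 0.99 | 5.3% | 5.1% | 5.1% | 86.5% | 85.5% |
| 0.1 | 6.29 | 6.02 | 1.04 | 3.8% | 3.6% | 5.0% | 88.7% | 89.5% |
| 0.2 | 6.31 | 5.79 | 1.09 | 3.1% | 2.7% | 4.9% | 88.4% | 92.5% |
| 0.3 | 6.31 | 5.67 | 1.11 | 2.8% | 2.7% | 5.4% | 89.8% | 95.4% |

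Standard errors and type I error are from runs with no treatment effect; power is at a difference of 20.

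A separate simulation under the same assumptions gave unadjusted type I error of 4.8 / 4.3 / 3.4 / 2.3% for R² = 0 / 0.1 / 0.2 / 0.3. Its power was 86 / 87 / 88 / 91% unadjusted against 85 / 88 / 92 / 96% adjusted.

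**4. The planned evaluable number, N = 32.** Power unadjusted against adjusted is 79.2 against 77.2% at R² = 0, 78.3 against 79.4% at 0.1, 81.0 against 85.4% at 0.2, and 82.0 against 88.9% at 0.3.

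**5. Cost in degrees of freedom.** Stage takes 2, location 1 and age 1, so 4 in all. Residual degrees of freedom at N = 40 fall from 38 to 34.

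**The case against.** The strongest reply is that the effect depends entirely on the factors being prognostic, and nothing in the document says that stage, location or age predicts GIQLI or NRS scores up to day 28. Eligibility also narrows two of them, to left-sided tumours and to clinical stages I to III, so a low R² is plausible. This stands. It is why the point is conditional and why R² = 0 is shown.

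Second, the error is in the safe direction. Unadjusted power at N = 40 stays above 85% at the planned effect, so what is forgone is extra precision rather than the power the trial was sized for. This stands too.

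Third, this is a condensed article, and an analysis plan that is not shown could specify covariates. This stands only in part. The article is not silent: it names the tests for every primary and secondary endpoint, although it does not rule out adjusted analyses in addition.

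Fourth, the calculations cover the t and Wilcoxon tests only. The chi-square and Fisher tests were not examined, and a linear model would not serve the categorical endpoints. This stands and limits the recommendation to the continuous primary endpoints.

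**Conclusion.** The stated analysis does not match the stated allocation. If the factors are prognostic, each unadjusted test of a continuous endpoint is conservative. At N = 40 its type I error is about 4% at R² = 0.1 and about 2-3% at R² = 0.3, and power at the planned difference is about 1 to 6 points below the adjusted model (up to about 7 at N = 32). If they are not prognostic, nothing is wrong and adjustment costs 1 to 2 points. These sizes rest on the assumed R², factor levels and allocation probability. The weight is minor to moderate.

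A reader might infer more than the document supports:

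- That the standard errors are certainly too large. This would need evidence that the factors are prognostic; being used for minimisation does not show it.
- That the treatment comparison is biased or false positives are inflated. Neither follows from this source.
- That the trial is under-sized because of this. The 32 and 40 are reproduced and need not change.
- That the trial as a whole runs below 5%. The figures are per test. The Endpoints section lists three primary endpoints, assessed at several postoperative times, so they say nothing about the overall error rate.

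**What to change.** In Statistical analysis, make the primary between-group comparison of GIQLI, NRS pain and NRS distention a linear model with treatment and the three minimisation factors as registered: TNM stage and tumour location as categories, age as continuous. Keep the unadjusted t or Wilcoxon test as a sensitivity analysis.

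The change is about one sentence and needs no new data. The registration centre must have the three factors in order to minimise on them, and Data collection assigns it the analysis. The downside is about 4 degrees of freedom and up to about 2 points of power if the factors turn out not to be prognostic. The categorical endpoints are outside this change.

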**Fig. 2 Fig2:**
[figure not shown]
Study flow chart. Investigators obtain informed consent from eligible patients before surgery. Patients are enrolled in the trial, if they can take medicine orally and have abdominal pain and/or distention at postoperative day (POD) 1. Enrolled patients are randomly assigned to either the Daikenchuto (DKT) or non-DKT group

### Treatment methods

#### Intervention group: DKT group

DKT (5 g) will be administered orally three times per day between POD 2 and POD 28. DKT manufactured by Tsumura & Co (Tokyo, Japan) will be used. We will monitor adherence by checking the number of doses of DKT that are not administered.

#### Control group: non-DKT group

No additional medicine will be administered as a comparator.

### Prohibited or limited drugs

Prohibited drugs will be drugs that are known to regulate intestinal movement (erythromycin, mosapride citrate, pantethine, panthenol, prostaglandin F2α), digestive enzyme preparations (diastase, pancreatin), anticholinergic drugs (atropine sulfate, scopolamine butylbromide), cathartic drugs (sodium picosulfate), antidiarrheal drugs (albumin tannate, aluminum silicate, dimethicone), antipsychotic drugs (diazepam, flunitrazepam), lactobacillus preparation (lactomin, lactic acid bacteriae, *Clostridium butyriam*), anti-Parkinsonian drugs, and contrast agent (gastrografin).

Limited drugs will be antiemetic drugs including metoclopramide and domperidone. Rescue drugs will be antidiarrheal drugs (magnesium oxides, sennoside), cathartic drugs (loperamide), and analgesic drugs (loxoprofen). If patients use the limited or rescue drugs, investigators will notate the dose and frequency.

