### Study design and setting

This study will be conducted at Kyoto University Hospital in Japan, and the design is an open-label randomized controlled trial. This study is expected to span a period of 2 years. Perioperative procedures in both groups will be performed based on the clinical path for laparoscopic colectomy in Kyoto University Hospital. All patients will receive standard bowel preparation (75 mg sodium picosulfate and 12 mg pursennid) and antibiotic prophylaxis (oral doses of 1 g kanamycin and 750 mg metronidazole), and surgical procedures will be conducted by well-experienced, board-certified laparoscopic colorectal surgeons at our institution. Except for the administration of DKT, treatment protocols including perioperative management and surgical procedures will be congruent among the intervention group (DKT group) and the control group (non-DKT group).

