### Endpoints

The following primary endpoints will be evaluated in this clinical trial: (i) grade of abdominal pain determined using the numeric rating scale (NRS), (ii) grade of abdominal distention determined using the NRS, and (iii) quality of life determined using the Gastrointestinal Quality Life Index (GIQLI) [9]. NRS measurements of abdominal pain and distention will be taken prior to surgery and at postoperative days (POD) 1, 4, 7, 14 and 28. GIQLI will be taken before surgery and at POD 14 and 28.

The secondary endpoints are (i) postoperative nutritional status (Onodera’s prognostic nutritional index (PNI) [10] and Controlling Nutritional Status score (CONUT score) [11]), (ii) time to initial flatus, (iii) time to initial defecation, (iv) bowel gas volume measured using analysis software, (v) character of stool (Bristol Stool Form Scale [12]), (vi) defecation frequency per day, (vii) postoperative complications (Clavien-Dindo classification [13]), (viii) duration of postoperative hospital stay, and (ix) metabolomics analysis of metabolites in stool and blood using gas chromatography-tandem mass spectrometry (GC/MS/MS) and liquid chromatography-tandem mass spectrometry (LC/MS/MS) (Fig. 1).

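### The rescue-drug sentence puts both bowel-drug class labels on agents of the opposite action, and the same two classes are prohibited one paragraph earlier

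*Protocol article*

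**What the plan says.** The section Prohibited or limited drugs in the Protocol article sets three tiers.

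- **Prohibited.** The list opens with "Prohibited drugs will be drugs that are known to regulate intestinal movement", followed by bracketed agents, and goes on through further classes. Among them are "cathartic drugs (sodium picosulfate), antidiarrheal drugs (albumin tannate, aluminum silicate, dimethicone".
- **Limited.** "Limited drugs will be antiemetic drugs including metoclopramide and domperidone".
- **Rescue.** "Rescue drugs will be antidiarrheal drugs (magnesium oxides, sennoside), cathartic drugs (loperamide), and analgesic drugs (loxoprofen".

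For the last two tiers the recording rule is: "If patients use the limited or rescue drugs, investigators will notate the dose and frequency".

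One other section bears on the labels. Study design and setting describes "standard bowel preparation (75 mg sodium picosulfate and 12 mg pursennid", given to all patients before surgery.

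**The concern.** This is an operative treatment rule: it tells staff what may be given to a patient between surgery and POD 28. Two things are wrong with it as written.

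First, the rescue labels and the drugs beside them point in opposite directions. Someone who works from the label would reach a drug with the opposite effect on the bowel. The patients have just had a colectomy, are enrolled on POD 1 because of abdominal symptoms, and are in a trial motivated by postoperative ileus.

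Second, cathartic and antidiarrheal drugs are each prohibited and, one paragraph later, offered as rescue. Unless the bracketed agents are the complete list, the rule gives two answers for any other drug in those classes.

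The endpoints make this relevant to the analysis as well. The secondary endpoints include "v) character of stool (Bristol Stool Form Scale [12]), (vi) defecation frequency per day", on which laxatives and antidiarrheals act. Two of the primary endpoints, distention on the NRS and the GIQLI score, could plausibly respond too. The trial is open-label with 20 patients planned per group, and Study design and setting promises the same management in both groups apart from Daikenchuto. That promise needs one unambiguous concomitant-drug rule.

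**Working it through.** No figure in the plan depends on this point, so the check compares the lists by class label and by named agent.

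**Step 1. Set the two bowel-active classes side by side.**

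| Class label | Agents in the prohibited list | Agents in the rescue list | Action of the rescue agents |
|---|---|---|---|
| Cathartic | sodium picosulfate | loperamide | antidiarrheal |
| Antidiarrheal | albumin tannate, aluminum silicate, dimethicone | magnesium oxides, sennoside | laxative |

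The last column is general pharmacology; the article does not state it.

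**Step 2. Count the mismatches.** The rescue list has three labels. The analgesic label fits loxoprofen. The other two do not fit their agents: 2 of 2 bowel-active labels, covering three named agents.

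**Step 3. Look for support inside the document.** For sennoside there is indirect support. The bowel preparation pairs pursennid, a sennoside product, with sodium picosulfate, which the prohibited list itself calls cathartic. The article does not say what pursennid contains, and it offers nothing comparable for magnesium oxide or loperamide.

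**Step 4. Compare named agents across lists.** The prohibited list names 19 agents: 5 for intestinal movement, 2 digestive enzymes, 2 anticholinergics, 1 cathartic, 3 antidiarrheals, 2 antipsychotics, 3 lactobacillus preparations and 1 contrast agent (5 + 2 + 2 + 1 + 3 + 2 + 3 + 1 = 19). The rescue list names 4. The overlap is 0 agents and 2 class labels.

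**Step 5. Ask what status follows for each kind of drug.**

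- *If the brackets are exhaustive:* every named agent has one status. A laxative or antidiarrheal named nowhere is on neither list.
- *If the brackets are examples:* an unnamed agent of either class is prohibited by one sentence and allowed as rescue by the next.

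The text does not choose between these, and its wording gives mixed signals. The limited tier marks its drugs as examples with the word including, and the brackets elsewhere carry no such word, which suggests complete lists. But anti-Parkinsonian drugs are prohibited with no agent named, so at least one entry works as a whole class.

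**Step 6. Check whether a plain swap changes what is available.** Exchanging the two labels, or exchanging the agents between them, leaves the same three bowel-active rescue agents. If the error is only a swap, the set of named rescue drugs is unaffected, and the harm is confined to anyone who acts on the label.

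**The case against.** The strongest reply is that drug names are printed beside every rescue label, so a clinician would have to ignore the name to go wrong. The article is also a condensed text, the swap may be a slip in writing or translation, and the full protocol may have it right. All of this is fair and limits the likely harm. It does not make the sentence correct. Recruitment had been under way since September 2016 according to Trial status, which is a reason to confirm that the working materials are right.

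Several stronger readings are tempting, and the document does not support them.

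- *A reader might infer that particular drugs are both banned and allowed.* None is: the overlap of named agents is zero. The double status exists only at class level.
- *A reader might infer that metoclopramide and domperidone contradict the ban on drugs that regulate intestinal movement.* They are placed by name in a separate tier and are absent from that ban's bracketed list. This reads as a deliberate assignment.
- *A reader might infer that the bowel preparation conflicts with the ban on sodium picosulfate.* The preparation precedes surgery, whereas enrolment is on POD 1 and treatment starts on POD 2. It serves only as evidence about a label.
- *A reader might infer that rescue use has been miscoded.* Nothing in the article says drug use is coded by class. Noting dose and frequency most naturally means noting them for a specific drug.
- *A reader might count the absence of a rescue-use table by arm as a gap.* That commonly belongs to the analysis plan, which is not shown.

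**Conclusion.** The point holds as an error in an operative rule. Both bowel-active rescue labels (2 of 2) are on agents of the opposite action, and two classes are listed as prohibited and as rescue without a statement that the bracketed agents are exhaustive. The status of any unnamed drug in those classes is therefore unclear.

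The conclusion on the labels rests on the ordinary pharmacology of three common drugs, with indirect support in the document for sennoside only. The conclusion on the classes rests on the text alone.

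It would go too far to say that the error directly moves the trial's endpoints. An effect on stool form and defecation frequency is possible, and one on distention and GIQLI is plausible, but only if someone acts on the wrong label or the unclear class rule is applied unevenly. The document gives no rate of rescue use, so the size cannot be determined. The sample size, randomization and planned tests do not depend on it. It still needs correction, because it bears on safety in postoperative patients and is cheap to put right.

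**What to change.** The sponsor's clinical lead should reconcile the prohibited, limited and rescue lists in Prohibited or limited drugs, so that:

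1. each named drug has one correct class label and one status;
2. the text states whether the bracketed agents are the complete list or examples;
3. site materials and the case report form are confirmed to match the reconciled text;
4. rescue use is recorded by drug name, with the dose and frequency already required.

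Which drugs are allowed remains the sponsor's clinical decision, and none is proposed here. If the full protocol is already correct, a correction to the article and the check in item 3 are enough.

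The cost is a wording correction and a site notice. No change to the sample size or the planned tests is needed.

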### Criteria for discontinuing the protocol treatment

If grade 3 postoperative adverse effects (Clavien-Dindo classification) are observed, the protocol treatment will be immediately discontinued.

### Data collection

Prospective data about all patients including physical examination, laboratory data, perioperative clinical information and complications will be collected. Personal information including names and chart numbers will not be collected. Only the study code will be collected and managed separately. The collected data will remain confidential until the investigators analyze the data. The final dataset will be managed by the chief investigator (KK). After the completion of the study, the collected data will be encrypted and stored for 10 years and then discarded. Data collection, management, analysis, and interpretation of data will be performed by the registration center (APO PLUS STATION Co., Ltd).

### Sample size determination

The sample size calculation is based on a primary endpoint, GIQLI. The GIQLI questionnaire containing 36 questions each with five response categories. The responses to questions are summed to give a numerical score (0–128 points). A previous report [9] indicates that the mean ± standard deviation (SD) change in the GIQLI score between two measurements before and 2 weeks after laparoscopic cholecystectomy in 194 patients was 17 ± 20.7 points. Therefore, the clinically significant mean difference in the GIQLI score is set at 20 with a SD of 20. Using a power level of 80% and a two-sided significance level of 5%, 32 patients (16 patients in each group) are required to show a difference between the DKT and non-DKT groups. Therefore, we determined that 40 patients (20 patients in each group) are needed to endure 20% dropout of patients from this trial.

### Statistical analysis

All analyses will be performed under the intention-to-treat principle. However, patients will be excluded from the analyses if they are proved to be ineligible after enrollment. Both primary and secondary endpoints will be compared between the DKT group and the non-DKT group. A two-tailed *P* value less than 0.05 is considered statistically significant. For continuous variables, the *t* test will be used when continuous variables follow a normal distribution, whereas the Wilcoxon rank-sum test will be used when continuous variables follow a non-normal distribution. For categorical variables, the chi-square test or Fisher’s exact test will be used according to the cell count.

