### Eligibility criteria

The eligible patients must satisfy the criteria defined below. Potential participants who meet the inclusion criteria will be recruited at outpatient clinics or during preoperative visits before surgery.

Inclusion criteria:Patients with left-sided colon cancer (including recto-sigmoid cancer) who are scheduled to undergo laparoscopic surgeryClinical stage I, II and IIIPatients who suffer from abdominal pain and distention at POD 1 (NRS score ≥1)The European Cooperative Oncology Group (ECOG) performance status of 2 or less.Patients aged 20 years and older at registrationPatients who can take medications orallyWritten informed consent provided to participate in the study

Exclusion criteria:Patients who have history of abdominal surgery or history of bowel obstructionPatients with concomitant inflammatory bowel disease such as ulcerative colitis and Crohn’s diseasePatients with concomitant endometriosisPatients requiring emergency surgeryPatients who have been or will be treated by chemotherapy or radiotherapyPatients with severe comorbidity such as cardiac disease, liver disease, pulmonary disease or renal diseasePatients who took Japanese herbal medicine (Kampo) up to 4 weeks prior to registrationPatients who took gastrointestinal prokinetic drugs, antipsychotic drugs or antidepressant drugs up to 4 weeks prior to registrationPatients with a history of a Kampo allergy in other formulationsPatients with hepatitis B or CPatients who are unable to take medications orally at POD 1Patients who are unsuitable for study inclusion as determined by the investigator (e.g., those with severe dementia)

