## Discussion

This trial will elucidate the effect of DKT on postoperative gastrointestinal symptoms following laparoscopic colectomy in patients with colon cancer. We mainly focus on two important topics: postoperative quality of life and postoperative metabolites in stool and blood.

Although several trials have been conducted, the clinical effectiveness of DKT is still unclear. In previous randomized controlled trials, all primary endpoints were objective outcomes, such as duration to initial flatus and incidence of postoperative paralytic ileus [14–18]. Although some patients were reported to be improved by DKT administration, there has been no report where any subjective outcomes (i.e., postoperative quality of life) are set up as primary endpoints. Assessment of postoperative quality of life has been conducted as a secondary endpoint in some trials, but there was no significant difference between the intervention group and control group [15–18]. This study is the randomized controlled trial to investigate the effects of DKT on postoperative subjective outcomes (i.e., postoperative quality of life) following laparoscopic colectomy as primary endpoints. Moreover, exploratory metabolomics analysis of metabolites in stool and blood will be conducted in this trial. It was reported that DKT could influence the microbiome of stool through bacterial metabolism in animals’ bowels [19, 20]. However, there is no report to date investigating this in humans. Using metabolomics analysis of metabolites in stool and blood, we plan to examine the effect of the intestinal flora by DKT administration, which can lead to the elucidation of the mechanism of DKT in gastrointestinal symptoms and the discovery of the biomarker candidates.

Therefore, we designed this trial to evaluate the effect of DKT on postoperative quality of life and postoperative metabolites in patients with colon cancer undergoing laparoscopic colectomy. The study aims to guide a future full-scale pragmatic randomized trial to assess the overall effectiveness of DKT to improve the postoperative quality of life following laparoscopic colectomy. Methodological rigor, including random allocation and prospective trial registration is aimed at reducing the risk of bias. As a limitation of this study, the possibility of insufficient sample size, bias in the open-label design, and the possibility of unblinding of the assessors to outcome may result in performance bias.

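### The analysis set is labelled intention-to-treat but drops randomised patients later found ineligible; in this open-label trial every randomised patient should be in the primary analysis

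*Protocol article*

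**What the plan says.** The protocol article, under Statistical analysis, opens with "All analyses will be performed under the intention-to-treat principle". The next sentence qualifies it: "However, patients will be excluded from the analyses if they are proved to be ineligible after enrollment". The qualification covers every endpoint, because it refers to the analyses in general.

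The timing comes from Registration: "Patients will be enrolled at POD 1". An eligibility form then goes to the registration centre, which randomises by minimisation on TNM stage, tumour location and age. Under Study design and setting, "the design is an open-label randomized controlled trial"; for the control arm, "No additional medicine will be administered as a comparator".

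Among the exclusion criteria are patients "who have been or will be treated by chemotherapy or" radiotherapy, and patients whom the investigator considers unsuitable for inclusion, with severe dementia as the example. Clinical stages I to III are eligible. Under Monitoring, two external people check eligibility in a sample of 10 patients at 6 months.

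**The concern.** An intention-to-treat analysis keeps every randomised patient in the arm assigned. Removing some of them after randomisation is safe only if the removal cannot depend on arm or outcome. Here patients and staff know the arm, and the written rule is not confined to facts that existed before randomisation. A criterion that looks forward in time can be settled after allocation, when the patient's early course is also known. If removals were related to both arm and outcome, the comparison would no longer be protected by randomisation. In a trial of 40, each patient removed is 1/20 = 5% of an arm, so a few removals could matter.

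**Working it through.** **1. Does the rule remove randomised patients?** Yes. Enrolment is on day 1 and central randomisation follows from the eligibility form. A patient found ineligible after enrolment will in general already have an assigned arm.

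**2. Which criteria can be settled after the arm is known?**
- Age, clinical stage, previous abdominal surgery or obstruction, inflammatory bowel disease, hepatitis, recent drug use, oral intake and day 1 symptoms are all facts existing by day 1. The risk is low if both arms are checked alike.
- Future chemotherapy or radiotherapy is open. The wording can mean treatment planned at registration or treatment given later; under the second reading, eligibility is settled after allocation.
- Investigator-judged unsuitability is mainly an entry judgement, but it is a judgement and could be revisited.
- Symptoms at day 1: Eligibility criteria require both pain and distention, while the Fig. 2 legend accepts either. The scores precede allocation, so this is not a post-allocation criterion. It does leave unclear whether a patient with one symptom counts as ineligible.

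**3. The plan's own sample size.** Inputs from Sample size determination: difference 20, SD 20, two-sided 5%, power 80%, 20% dropout.
- n per arm = 2 × (1.960 + 0.842)² × 20² / 20² = 15.7, rounded up to 16, so 32 in total.
- 32 / (1 − 0.20) = 40, or 20 per arm.

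Both figures reproduce by the normal approximation. By the exact t calculation, power is 78.1% with 16 per arm and 86.9% with all 20 per arm evaluable, so keeping everyone needs no extra patients.

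**4. How far could exclusions move the result?** The article gives no expected number of exclusions, so 1 to 4 are assumed, all from one arm of 20, with normal scores, SD 20 and no true effect.

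Worst case, the k lowest scorers removed: expected shift = 20 × (sum of the k largest expected normal order statistics for n = 20) / (20 − k). The first four are 1.867, 1.408, 1.131 and 0.921.
- k = 1: 20 × 1.867 / 19 = 1.97
- k = 2: 20 × 3.275 / 18 = 3.64
- k = 3: 20 × 4.406 / 17 = 5.18
- k = 4: 20 × 5.327 / 16 = 6.66

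Milder case, k removed at random from the worse-scoring half: expected shift = 20 × k × 0.767 / (20 − k), where 0.767 is the mean distance, in SDs, of the lower ten values below the centre.

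The type I errors come from 100,000 simulated trials (t test, two-sided 5%), whose mean shifts agree with these formulas to within 0.03 points.

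| Removed from one arm | Worst case: shift, type I error | Worse half at random: shift, type I error |
|---|---|---|
| 1 | 2.0 points, 6.8% | 0.8 points, 5.0% |
| 2 | 3.6 points, 10.2% | 1.7 points, 5.4% |
| 3 | 5.2 points, 14.5% | 2.7 points, 6.3% |
| 4 | 6.6–6.7 points, 19.8% | 3.8 points, 8.0% |

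Against the 20-point target, the worst-case shift for one to three removals is 2.0/20 = 10% to 5.2/20 = 26%. Where removal is unrelated to outcome, the expected shift is zero and the simulated error stays at about 5% (5.0% with two removed, 4.9% with four); only precision is lost.

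**The case against.** The strongest reply is that the exclusion is openly disclosed. The second sentence is a stated exception to the first, and an analyst would know what to do. That is right: the two sentences are not incompatible instructions. What remains is that the label does not fit the set, and that no analysis of all randomised patients is described.

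Second, an article may leave to a fuller document who decides on exclusions, by when and whether blind. That also stands, and the absence of such procedures is not the complaint. The complaint is about a rule that the article does state, which removes randomised patients from the analyses.

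Third, ineligibility must be proved, and nearly all criteria are facts fixed by day 1. This narrows the exposure to the chemotherapy/radiotherapy clause and, less so, investigator judgement.

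Two stronger readings are tempting:
- A reader might infer that chemotherapy-based exclusions would undo the minimisation on TNM stage, since they would fall on higher stages. The documents do not support this. Minimisation should leave the arms similar in stage, so removals by stage would take similar numbers from each; balance is lost only if the rule is applied differently by arm.
- A reader might infer that the differing symptom wording allows exclusion by arm. It concerns scores taken before allocation, so it is an ambiguity about eligibility only.

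Finally, the Discussion already concedes "bias in the open-label design, and the possibility of unblinding of the assessors to outcome may result in performance bias", and presents the trial as a guide to a larger one. That acknowledges open-label bias in general, but not bias through the choice of analysis set.

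**Conclusion.** The point holds in limited form. The planned set is modified intention-to-treat under an intention-to-treat label, and the rule permits, in an open-label trial, exclusions decided after allocation is known. The text does not show that such exclusions will happen or that bias will result.

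The size is unknown. The worst-case shift of about 2.0 to 5.2 points for one to three exclusions requires that every removed patient be a lowest scorer and that all come from one arm. Partial dependence on outcome gives less, and independence gives none. All of these figures rest on assumed numbers of exclusions and on the plan's SD of 20.

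This should be fixed: the rule governs every endpoint and the correction is cheap. The evidence does not support calling it a demonstrated bias.

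**What to change.** - Make all randomised patients, analysed in the arm assigned, the primary analysis set, including any later found ineligible.
- Move the exclusion for ineligibility to a sensitivity analysis. Limit it to facts dated before randomisation, have it judged by someone unaware of arm and outcome, and report the number and reasons by arm.
- Ask the sponsor to clarify at what time point the chemotherapy/radiotherapy criterion is judged, so that it can be applied consistently with the exclusion rule. Which reading is intended is for the sponsor to say.
- Reconcile the pain and distention wording in Eligibility criteria with that in the Fig. 2 legend.

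The cost is a sentence or two of text and one sensitivity analysis, with no additional patients. The downside is that a few ineligible patients may slightly dilute the estimated effect.
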